## Abstract

**Purpose:**

The aim of this study is to investigate the effect of comprehensive rehabilitation on apnea hypopnea index (AHI) in patients with obstructive sleep apnea (OSA).

**Methods:**

Patients diagnosed with OSA and meeting the eligibility criteria will be randomly allocated in the groups. The experimental group will receive comprehensive rehabilitation, and the control group will receive myofunctional therapy. CPAP will be continued by all the participants. Both the groups will receive the interventions for 12 weeks. The primary outcome measures are AHI and Epworth Sleepiness Scale (ESS), and secondary outcomes are Pittsburg Sleep Quality Index (PSQI), Oxygen Desaturation Index (ODI), Snoring Index (SI), Manual Assessment of Respiratory Motion (MARM), Breath Hold Test (BHT), and Self Evaluation of Breathing Questionnaire (SEBQ). The outcomes will be assessed at baseline and at the end of 12 weeks. A follow-up will be taken at the end of 24 weeks. Power analysis suggests that enrollment of 118 patients will required. Repeated measures ANOVA will be used to analyze the effect of the intervention.

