## Method

### Study design

The study design for the current protocol is an “assessor-blinded parallel group randomized controlled trial.” The trial will use the “Consolidated Standards of Reporting Trials (CONSORT) guidelines” [14]. All outcomes will be assessed at baseline and at the end of 12 weeks. Additionally, a follow-up will occur at the end of 24 weeks with assessment of daytime sleepiness, sleep quality, and breathing pattern dysfunction. The study flow is shown in Fig. 1. Reporting of the protocol is done according to the “Standard Protocol Items: Recommendations for Intervention Trials (SPIRIT) guidelines” [15]. The present study is approved by Institutional Research Committee (IRC) of Manipal Academy of Higher Education. Scientific Committee approval and ethical clearance to conduct the study is obtained from Manipal Hospital, Bangalore. The study is registered in Clinical Trials Registry–India (CTRI) (registration number—CTRI/2023/10/058486).

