### Outcomes

AHI and ESS will be the primary outcomes. Secondary outcomes will be Oxygen Desaturation Index, Snoring Index, Pittsburgh Sleep Quality Index, Manual Assessment Of Respiratory Motion, Breath Hold Test, and Self Evaluation of Breathing Questionnaire.

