## Results

Statistician will be provided deidentified data, and analysis will be performed. Descriptive statistics (frequency tables and percentages for categorical variables and for computation of prevalence) will be used.

Mean/median and standard deviation/inter-quartile range will be analyzed after exploring skewness for the quantitative variables. Repeated-measures ANOVA or its non-parametric variants will be used after exploring the model assumptions to assess the effectiveness of the intervention. Correlation analysis may be done to explore associations between the outcomes.

Regression models may be used for adjustment of covariates to account the confounding factors and for unbiased treatment effect. Intention to treat analysis will be used to manage missing data. Inferential statistics will be used for exploratory data analysis.

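### The only committed efficacy analysis, repeated-measures ANOVA, treats baseline as an outcome; a baseline-adjusted week-12 comparison would be more precise and clearer at no cost in data

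*Protocol article*

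**What the plan says.** The abstract (Methods) of the protocol article commits to one efficacy method: "Repeated measures ANOVA will be used to analyze the effect of the intervention". The Results section, which holds the analysis plan, says the same with a fallback: "Repeated-measures ANOVA or its non-parametric variants will be used after exploring the model assumptions to assess the effectiveness of the intervention". Neither place says whether the group, time or group-by-time term carries the inference, or at which visit.

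Covariate adjustment is optional: "Regression models may be used for adjustment of covariates to account the confounding factors and for unbiased treatment effect". The baseline value of the outcome is not named as a covariate.

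On outcomes and timing:
- Outcomes section: "AHI and ESS will be the primary outcomes".
- Study design: "All outcomes will be assessed at baseline and at the end of 12 weeks". It then adds that "a follow-up will occur at the end of 24 weeks with assessment of daytime sleepiness, sleep quality, and breathing pattern dysfunction". AHI is not in that list.
- Abstract: "Both the groups will receive the interventions for 12 weeks". Week 24 is therefore 12 weeks after the end of treatment.

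**The concern.** Repeated-measures ANOVA places the baseline value in the outcome vector. Randomisation makes the expected baseline difference between arms zero, so each term of the model answers a different question:

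- The **group main effect** averages that zero into the treatment effect and dilutes it.
- The **time effect** compares no arms.
- The **group-by-time effect** is a treatment comparison. With two visits it is the t-test on change. With three it is a 2-df omnibus test that does not isolate week 12.

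None of these is a week-12 difference adjusted for baseline, which the data already planned would support. At stake are precision on both primary outcomes and, for ESS, which treatment effect the primary p-value refers to.

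**Working it through.** **The plan's own figure.** The sample size section gives 116.25 with 20% drop-out and a design effect of 1.5. Back-solving, 116.25 × 0.8 / 1.5 = 62 exactly.

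For the group main effect of a repeated-measures ANOVA with m visits, the noncentrality is lambda = N f² m / (1 + (m−1)r), on 1 and N−2 df. Read 0.30 as f and take m = 3 and r = 0.5:
- N = 62: lambda = 62 × 0.09 × 3 / 2 = 8.37, power 81.2%.
- N = 60: lambda = 8.10, power 79.9%.

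So 62 is the smallest even total that reaches 80%. Other readings tried do not give 62: two visits at r = 0.5 gives 68, group-by-time with three visits at r = 0.5 gives 20, and one-way ANOVA gives 90. The sample size therefore appears to rest on the three-visit group main effect. That is an inference; the article states neither the metric of 0.30, nor m, nor r.

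**Inputs for the comparison.** Completers per arm: 59 × 0.8 = 47.2, taken as 47. Assumed, because the article gives no value: a week-12 effect D = 0.5 SD, a correlation rho of 0.3, 0.5 or 0.7 between visits, equal variances (SD 1) and compound symmetry. Tests are two-sided at 5%.

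**Two visits (AHI).** The variance of the arm difference is 2/n times:
- change score, identical to group-by-time: 2(1−rho), estimating D;
- ANCOVA: 1−rho², estimating D;
- group main effect: (1+rho)/2, estimating D/2.

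The ANCOVA/change variance ratio is (1−rho²) / [2(1−rho)] = (1+rho)/2.

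| | rho 0.3 | rho 0.5 | rho 0.7 |
|---|---|---|---|
| ANCOVA/change variance | 0.65 | 0.75 | 0.85 |
| Power, group main effect | 32% | 28% | 26% |
| Power, group-by-time | 53% | 67% | 87% |
| Power, ANCOVA | 71% | 79% | 92% |

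Worked case at rho = 0.5: for group-by-time, 0.5 / √(2/47 × 1.0) = 2.42, power 67%. For ANCOVA, 0.5 / √(2/47 × 0.75) = 2.80, power 79%.

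**Three visits (ESS and the other week-24 outcomes).** Arm differences at the three visits are (0, D, gD), where g is the share of the effect left at week 24.
- The group main effect estimates D(1+g)/3, that is 0.67D if the effect persists (g = 1) and 0.50D if it halves (g = 0.5). Its variance is 2/n × (1+2rho)/3.
- The 2-df interaction has lambda = (n/2) × (sum of squared centred differences) / (1−rho). At rho = 0.5 this is 23.5 × 0.1667 / 0.5 = 7.83 if the effect persists, and 23.5 × 0.125 / 0.5 = 5.88 if it halves.

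| Power | rho 0.3 | rho 0.5 | rho 0.7 |
|---|---|---|---|
| Interaction, effect persists | 55% | 70% | 90% |
| Interaction, effect halves | 43% | 57% | 80% |
| Main effect, effect persists | 59% | 50% | 43% |
| Main effect, effect halves | 38% | 31% | 27% |
| Week-12 ANCOVA | 71% | 79% | 92% |

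**The case against.** The strongest reply is that the group-by-time test is a legitimate randomised comparison, and that a condensed article may leave the choice of term and contrast to an analysis plan that is not shown. Both parts have weight. Leaving the term unnamed is not in itself a fault here. What can be criticised is the method the article does commit to, and for that method ANCOVA is more precise than the change comparison at every rho below 1.

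A reader might infer that repeated-measures ANOVA misses the 12-week effect altogether. For AHI the document does not support this. The study design section lists no week-24 AHI, so no visits are mixed, and group-by-time is exactly the comparison of 12-week change. The randomisation section speaks more loosely of outcome collection at 24 weeks, but the study design section is the specific text.

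A reader might also infer that a time effect would be reported as efficacy, or that the optional regression would adjust for CPAP compliance. The article says neither. Compliance is recorded and defined, and is not proposed as a covariate.

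The size of the gain is also open. At rho = 0.7 it is 5 points (87% to 92%). If the ESS effect persists to week 24, the omnibus test at rho = 0.5 (70%) slightly exceeds the two-visit change test (67%), though not ANCOVA (79%). The 0.5 SD effect and every rho are assumptions.

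**Conclusion.** The point holds as one of efficiency and clarity of estimand. It alleges neither bias nor an inflated type I error.

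For AHI, moving from group-by-time to ANCOVA raises power by about 18, 12 and 5 points at rho 0.3, 0.5 and 0.7. If the group main effect were the test, as the sample size arithmetic suggests but does not establish, the 12-week effect would be halved and power would be about 26 to 32%.

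For ESS and the other outcomes measured at week 24, both between-arm terms combine the end-of-treatment visit with one 12 weeks after treatment, and both have less power than week-12 ANCOVA in every case tabulated.

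These powers rest on 47 per arm, a 0.5 SD effect, equal variances and compound symmetry. The direction of the ANCOVA/change comparison needs only equal variances at the two visits and rho below 1; its size depends on rho.

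**What to change.** In the abstract and the Results section, replace the repeated-measures ANOVA statement with wording such as: *The primary analysis for each primary outcome is the between-arm difference at week 12 with its 95% confidence interval, adjusted for the baseline value of that outcome. AHI will be analysed by ANCOVA; ESS by ANCOVA or by a mixed model with baseline as covariate and a week-12 contrast. The week-24 difference is a separate secondary contrast. Any further adjustment covariates will be variables measured before randomisation.*

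The last sentence replaces the open-ended regression statement. The sample size paragraph should then say which test and effect metric it refers to.

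The cost is wording only: no added patients, visits or measurements.

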**Conclusion:**

By performing this research, we may develop insights on a novel comprehensive approach for treatment of patients with OSA.

**Trial registration:**

CTRI/2023/10/058486.

## Introduction

Obstructive sleep apnea (OSA) presents with arousals from sleep at night due to collapse of oropharyngeal airway. OSA commonly results in excessive daytime sleepiness [1, 2]. Loud snoring, choking, and gasping during sleep are reported by the bed partners of these individuals with OSA [3]. The breathing pattern in OSA shows predominant thoracic breathing with a paradoxical motion of the abdomen [1, 4]. Patients with OSA tend to have oral and oro-nasal breathing in sleep [5].

The episodes of hypopnea and apnea during sleep are measured by polysomnography or home sleep testing with apnea hypopnea index (AHI) being a vital measure of the test [6]. Pharmacological management of OSA is not approved [7]. However, a recent systematic review [8] concluded that pharmacological treatment can be used as an adjunct therapy though it has only mild to moderate effect on OSA severity. Medications for OSA have potential negative effects. Hence, non-pharmacological management involving continuous positive airway pressure (CPAP) is considered to be the first line of treatment [9]. Evidence has shown the effectiveness of CPAP in decreasing the severity of OSA and improving sleep quality [10]. However, effects of CPAP may result in decreased adherence to treatment [2].

Myofunctional therapy serves as an adjuvant treatment for OSA. Myofunctional therapy involves isotonic and isometric oropharyngeal exercises, targeting the tongue and pharyngeal musculature [11]. A recent systematic review [12] has established the positive effects of myofunctional therapy in OSA. Another study, [13] showed the effectiveness of functional nasal breathing rehabilitation techniques on patients with nasal obstruction and mouth breathing. These patients reportedly decreased mouth breathing, reduced snoring, and improved sleep [13]. Therefore further studies are needed on this technique in patients with impaired sleep.

To date, publications have reported on the usefulness of CPAP and myofunctional therapy as treatment approaches for OSA. Thus, a randomized controlled trial to assess the effectiveness of comprehensive rehabilitation for OSA is justifiable. The aim of the study is to investigate the effect of comprehensive rehabilitation on AHI in patients with OSA. The primary objectives of the study are to determine the effect of comprehensive rehabilitation on AHI and excessive day time sleepiness. The secondary objectives are to determine effects on oxygen desaturation, snoring, sleep quality, and on the components of breathing dysfunction.

## Method

### Study design

The study design for the current protocol is an “assessor-blinded parallel group randomized controlled trial.” The trial will use the “Consolidated Standards of Reporting Trials (CONSORT) guidelines” [14]. All outcomes will be assessed at baseline and at the end of 12 weeks. Additionally, a follow-up will occur at the end of 24 weeks with assessment of daytime sleepiness, sleep quality, and breathing pattern dysfunction. The study flow is shown in Fig. 1. Reporting of the protocol is done according to the “Standard Protocol Items: Recommendations for Intervention Trials (SPIRIT) guidelines” [15]. The present study is approved by Institutional Research Committee (IRC) of Manipal Academy of Higher Education. Scientific Committee approval and ethical clearance to conduct the study is obtained from Manipal Hospital, Bangalore. The study is registered in Clinical Trials Registry–India (CTRI) (registration number—CTRI/2023/10/058486).

**Fig. 1 Fig1:**
[figure not shown]
Study flow chart

### Participant recruitment, sample size, and eligibility criteria

According to the American Academy of Sleep Medicine (AASM) criteria, participants will be diagnosed with OSA by the consultant pulmonologist [16]. The recruitment of the participants will take place at Manipal Hospital, Bangalore, from October, 2023, to February, 2026.

The sample size was calculated at 5% level of significance with 80% power and an effect size of 0.30. The drop-out rate (20%) and the design effect (1.5) were also incorporated. Thus, the sample derived was 116.25 and 118 will be enrolled, with 59 in each group. The eligibility criteria are outlined in Table 1.

**Table 1 Tab1:** Eligibility criteria

Inclusion criteria	Exclusion criteria
Mild and moderate OSA (AHI ≥ 5 to ≤ 30)	Obstructive nasal diseases
Age 25 to 65 years	Craniofacial malformations
Either gender	Comorbid sleep disorders such as insomnia, restless leg syndrome
BMI less than 40 kg/m^2^	Pregnant women
	History of pharyngeal surgery
	History of congestive heart failure, cardiomyopathy, chronic obstructive pulmonary disease, and liver cirrhosis
	History of neuromuscular disorders such as myasthenia gravis, motor neuron disease, and demyelinating diseases
	History of stroke
	Psychiatric illness
	Consumption of alcoholic beverages (more than 3 oz/day or more than 2 alcoholic beverages/day)
	Periodontal disease (gingivitis]
	Temporomandibular joint dysfunction

### Randomization, allocation, and blinding

The randomization will be done using computer-generated block randomization. Allocation will be done using sealed envelopes. The allocation sequence will be kept safely in “sequentially numbered opaque sealed envelopes.” The eligible participants will be informed about the trial process by the principal investigator and an informed consent will be sought. A blinded assessor will collect outcome measures at baseline, at the end of 12 weeks, and at the end of 24 weeks. The treatment will be given to the participant by the therapist according to that mentioned in the sealed envelope.

### Intervention

#### CR group: comprehensive rehabilitation + CPAP

The comprehensive rehabilitation for OSA will include 3 components: functional nasal breathing rehabilitation, oropharyngeal exercises (myofunctional therapy], and diaphragmatic breathing exercise.

#### Functional nasal breathing rehabilitation [13]

This technique will include three exercises, including breath hold, humming and its variation, and nose open smile. A rest interval of 2 min will be given between each exercise. All exercises will repeated 5 times.

#### Oropharyngeal exercises [17]

These maneuvers include soft palate exercises, tongue exercises, facial exercises, and stomatognathic functions. Each exercise will be repeated 5 times. Isometric exercise of the muscles will be performed with 10-s hold. For stomatognathic functions, the subject will be advised to perform balloon blowing exercises and to chew bilaterally while having food.

#### Diaphragmatic breathing exercise [18]

This exercise will be performed 5 times by the subject.

This protocol will be followed 3 times per day for 5 days per week for 12 weeks. The treatment will be supervised for the 1st week. From the 2nd week, weekly supervised sessions will be held with the participants. A weekly exercise diary will be provided to the patients to document their adherence to treatment.

#### MFT group: myofunctional therapy + CPAP

The myofunctional therapy will include the oropharyngeal exercises of soft palate, tongue, and face as outlined above. Myofunctional therapy will be performed 3 times per day, 5 days per week for 12 weeks.

CPAP treatment will be given to the subjects daily in both the groups for 12 weeks. The CPAP prescription will be followed as directed by the pulmonologist. CPAP data will be noted to record compliance. Compliance will be defined as use of the CPAP for ≥ 4 h per night for at least 70% of nights in the 12 weeks will be followed [19].

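### As written, the control arm's myofunctional therapy lists three of the four elements given in the experimental arm; stomatognathic functions are missing from it

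*Protocol article*

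**What the plan says.** The Methods paragraph of the Abstract sets out the contrast: "The experimental group will receive comprehensive rehabilitation, and the control group will receive myofunctional therapy". Both arms continue CPAP.

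Under the CR group heading, the experimental package has three components: functional nasal breathing rehabilitation, "oropharyngeal exercises (myofunctional therapy"), and diaphragmatic breathing. The bracket makes the two terms synonyms.

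The subsection on oropharyngeal exercises then gives their content: "These maneuvers include soft palate exercises, tongue exercises, facial exercises, and stomatognathic functions". It explains the fourth element: "For stomatognathic functions, the subject will be advised to perform balloon blowing exercises and to chew bilaterally while having food".

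Under the MFT group heading, the control treatment is described as follows: "The myofunctional therapy will include the oropharyngeal exercises of soft palate, tongue, and face as outlined above". The frequency and duration match the CR arm: three times a day, five days a week, for 12 weeks.

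**The concern.** The control arm is meant to receive myofunctional therapy, and the CR arm is meant to receive the same therapy plus two further components. That makes the myofunctional therapy the shared part, and it should be identical in both arms. The article instead gives the control arm its own list, and that list is shorter than the article's definition of the therapy.

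This matters for interpretation. The Discussion rests its hypothesis on nasal rehabilitation and diaphragmatic breathing. If control patients do no balloon blowing and are not told to chew bilaterally, a benefit of CR over MFT could come from those activities, from the two intended components, or from both. The data could not separate these sources. The label on the control arm would also be inexact, since it would hold only part of what the article itself calls myofunctional therapy.

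**Working it through.** No formula applies, because the point depends on no sample size, power or error rate. The check is to compare the elements listed for each arm.

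| Element | CR arm | MFT arm, as written |
|---|---|---|
| Soft palate | listed | listed |
| Tongue | listed | listed |
| Face | listed | listed |
| Stomatognathic functions (balloon blowing, bilateral chewing) | listed | not listed |
| Functional nasal breathing rehabilitation | listed | not listed (intended difference) |
| Diaphragmatic breathing | listed | not listed (intended difference) |
| CPAP | listed | listed |

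1. The CR group section makes oropharyngeal exercises and myofunctional therapy the same thing, so the first four rows are the article's own definition of myofunctional therapy.
2. The CR arm has 4 of these 4 elements and the MFT arm has 3 of 4. The unmatched one is stomatognathic functions.
3. No other section of the article gives that element to the control arm. The Abstract and the MFT heading name the therapy without listing its content, so they neither restore nor exclude it.
4. On the literal reading, the CR-MFT contrast therefore contains three differences: nasal breathing rehabilitation, diaphragmatic breathing and stomatognathic functions. On the shorthand reading it contains the intended two.
5. The aim and the primary objectives concern comprehensive rehabilitation as a whole. On either reading, the randomised comparison estimates the effect of the whole CR package against whatever the control arm receives. Only attribution to the two added components depends on which reading is right.

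**The case against.** The strongest reply is that the control sentence is shorthand. It says that the therapy will *include* these exercises, it points back to the description above, and it uses a name that the article has already equated with the full set. No passage says that stomatognathic functions are withheld or gives a reason for withholding them. They are also worded differently from the rest: the first three are called exercises, whereas these are functions on which the patient is advised, so a condensed sentence could drop them by accident. The full protocol is not shown, and an article may leave exercise detail to it. This reply stands in part: a deliberate difference between the arms is not established. It does not remove the point, because the article states a list for the control arm that disagrees with its own definition, and a therapist working from that sentence would omit the fourth element.

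The second reply is that the harm is narrow. This stands. No stated objective or analysis attributes the effect to individual components, and the Discussion offers only a hypothesis about them.

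A reader might infer three stronger points, none of which the documents support.

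- **That the primary comparison is invalid.** It is not: the package effect remains estimable.
- **That the imbalance can be expressed as a dose.** A reader might apply "Each exercise will be repeated 5 times" to balloon blowing over 3 × 5 × 12 = 180 sessions and obtain 5 × 180 = 900 repetitions. But that instruction comes before the sentence on stomatognathic functions, which gives no number, and chewing has no stated dose at all. Comparing such a total with the breath holds, hums and diaphragmatic breaths in the CR arm would also treat unlike exercises as equal units.
- **That control patients get no supervised sessions and no exercise diary.** These are described within the CR section, but in general terms (participants, patients). The data monitoring section records non-adherence without limiting it to one arm. Silence in a condensed article does not show a difference.

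**Conclusion.** The point holds in a limited form and is minor. The article's control arm, as written, lists three of the four elements of the myofunctional therapy that the CR arm receives. If that list is followed literally, a CR-MFT difference in AHI or ESS could not be credited to nasal breathing rehabilitation and diaphragmatic breathing over the same myofunctional therapy. If the list is shorthand for the full set, only the wording is at fault; the article does not settle which is the case.

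The size is one unmatched element of four. Any effect of that element on AHI or ESS, and hence any share of a treatment difference due to it, cannot be derived from the article. The primary test, the sample size of 118 and the estimate of the package effect are not affected.

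**What to change.** Prescribe the full oropharyngeal list in both arms, naming balloon blowing and bilateral chewing in the MFT section. If both arms are already treated this way, one corrected sentence is enough.

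Recruitment is stated to run from October 2023 to February 2026, so control patients may already have been treated under the shorter list. If so, name stomatognathic functions as a third difference between the arms when the result is reported. Limit the conclusion to the package as delivered against the control as delivered, with no claim for the two breathing components alone.

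The cost is balloons and brief instruction for the 59 control patients. If stomatognathic functions have an effect of their own, matching them may make the between-arm difference smaller, by an amount that cannot be stated from the article. No sample size or analysis figure in the plan needs to change.

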#### Home sleep apnea testing (HSAT)

Home sleep apnea testing will be used to diagnose and measure severity of OSA as recommended by the American Sleep Disorders Association (ASDA) [20, 21]. According to Sleep, Cardiovascular, Oximetry, Position, Effort, and Respiratory (SCOPER) parameters, the HSAT that will be used can be denoted as denoted as S_0_, C_3_, O_1X_, P_2_, E_1_, and R_2_ [22]. HSAT has a high sensitivity (82%), specificity (88%), and positive predictive value of (89%) [21, 23].

The parameters measured are as follows:Apnea Hypopnea Index (AHI)—the average number of events of apnea and hypopnea per hour during sleep. AHI is used to determine the severity of OSA as mild (AHI 5 up to 15), moderate (AHI 15 up to 30), and severe (AHI 30 or more).Oxygen Desaturation Index (ODI)—the average number of episodes of oxygen desaturation per hour.Snoring Index (SI)—the measure of number of snoring events per hour during sleep.

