## Discussion

The current study includes functional nasal breathing rehabilitation along with myofunctional therapy and diaphragmatic breathing as a comprehensive management protocol for patients with OSA. Myofunctional therapy as a part of conventional treatment for OSA, in addition to CPAP, has reported to have a positive effect on the tone of oropharyngeal muscles and other soft tissues of the upper airway [11]. It may be hypothesized from the preceding research that functional nasal rehabilitation and diaphragmatic breathing exercise may be beneficial for patients with OSA [13, 18]. 

A limitation of this study as designed is that it will be performed in a specific region, and the data cannot be generalized to other populations and settings.

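### The only post-treatment AHI comes at the end of 12 weeks of daily CPAP and no exception is made for the test night, so it may be a residual or mixed value

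*Protocol article*

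**What the plan says.** All references are to the protocol article.

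- **Endpoint.** Outcomes: "AHI and ESS will be the primary outcomes".
- **Timing.** Study design: "All outcomes will be assessed at baseline and at the end of 12 weeks". The next visit is described thus: "Additionally, a follow-up will occur at the end of 24 weeks with assessment of daytime sleepiness, sleep quality, and breathing pattern dysfunction". That list contains neither AHI nor the other two home-sleep-test measures (ODI and Snoring Index). Week 12 is therefore the only post-treatment AHI.
- **CPAP.** The section on the MFT group: "CPAP treatment will be given to the subjects daily in both the groups for 12 weeks". The Methods paragraph of the abstract: "CPAP will be continued by all the participants". Compliance means at least 4 hours "per night for at least 70% of nights in the 12 weeks".
- **Measurement.** The HSAT section: "Home sleep apnea testing will be used to diagnose and measure severity of OSA". It defines AHI as a rate per hour of sleep and does not say whether CPAP is worn during the recording.
- **Entry range.** Table 1 admits patients with an AHI from 5 to 30.
- **Analysis.** The Results section names repeated-measures ANOVA or a non-parametric variant. Regression adjustment for covariates is mentioned only as something that may be done.

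**The concern.** The Introduction itself says that CPAP lowers OSA severity. If patients keep to the daily CPAP instruction on the night of the week-12 test, the recording shows what CPAP leaves over and not the AHI they would have without it. If some patients wear it all night, some for part of the night and some not at all, the recordings are not comparable with one another.

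Three things are at stake:

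- The between-arm AHI difference has less room to appear, because AHI cannot fall below zero.
- Differences in CPAP use on the test night add variance unrelated to the rehabilitation programme.
- The fall from baseline within each arm would mostly reflect CPAP, yet could be read as an effect of the exercises.

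No later AHI is scheduled that could repair this. ODI and Snoring Index come from the same recording and share the problem. ESS, the other primary outcome, is a questionnaire and does not depend on the test night.

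**Working it through.** **The plan's own figure.** The point concerns a measurement condition, so the sample size neither supports nor contradicts it. For completeness, 116.25 × 0.80 / 1.5 = 62, and 62 × 1.5 / 0.80 = 116.25, so the stated figure follows from a base of 62 patients. That base can be reached with f = 0.30, three measurements and a within-patient correlation of 0.5. The last two are assumptions that the article does not state. AHI has only two measurements.

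**Step 1: the schedule.** Daily CPAP covers 12 weeks in both arms. The AHI test falls at the end of those 12 weeks, and the 24-week list omits AHI. An off-CPAP test would need either an exception to the daily instruction or a recording just after the period ends. The article describes neither.

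**Step 2: the floor.** AHI is at least 0, so

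(MFT mean − comprehensive rehabilitation mean) ≤ MFT mean.

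If CPAP holds the MFT mean below 5 (assumed; 5 is the article's lower limit for mild OSA), the advantage of comprehensive rehabilitation must be below 5 events per hour. This bounds the absolute difference. It is not a statement about power, because the standard deviation would shrink as well.

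**Step 3: mixed nights, one patient.** Assumed: untreated AHI 20, 7 hours of sleep, AHI on CPAP 10% to 50% of untreated (2 to 10).

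| Test night | AHI recorded |
|---|---|
| No CPAP | 20 |
| CPAP for 4 of 7 hours | (3 × 20 + 4 × 2)/7 = 9.7 to (3 × 20 + 4 × 10)/7 = 14.3 |
| CPAP all night | 2 to 10 |

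The same patient with the same underlying disease could record anything from 2 to 20.

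**Step 4: the analysis.** With two time points, the group-by-time test of a repeated-measures ANOVA is the test of unadjusted change scores. Let the baseline standard deviation be s, the off-CPAP treatment difference be D and the within-arm correlation be r. Suppose CPAP multiplies every week-12 AHI by the same factor c, with baseline off CPAP. Signal over standard deviation is then:

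- change score: cD / (s√(1 + c² − 2rc))
- week 12 adjusted for baseline: cD / (cs√(1 − r²)) = D / (s√(1 − r²)), which does not depend on c.

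With r = 0.5 (assumed), in units of D/s:

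| c (assumed) | Change score | Baseline-adjusted |
|---|---|---|
| 1 (off CPAP) | 1/√1 = 1.00 | 1/√0.75 = 1.15 |
| 0.5 | 0.5/√0.75 = 0.58 | 1.15 |
| 0.1 | 0.1/√0.91 = 0.10 | 1.15 |

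This is an illustration and does not estimate the loss in this trial. It shows that uniform compression harms a change-score analysis and leaves a baseline-adjusted one intact. If c varies between patients or nights, as in Step 3, residual variance rises and the adjusted analysis loses precision too.

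**The case against.** The strongest objection is that the case rests on silence. Nowhere does the article say that the week-12 test is recorded on CPAP. The HSAT section speaks of diagnosis and severity, quotes diagnostic accuracy and gives the usual severity bands, all of which suit a recording without CPAP. A test just after the 12 weeks would also fit the schedule. Test-night instructions are the kind of detail that a condensed article leaves to the full protocol.

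Much of this stands, and a reader should not infer that the trial measures AHI on CPAP. What remains is that the article is not merely silent: it gives a daily CPAP instruction running up to the only post-treatment AHI and says that all participants continue CPAP. Someone following the text would not know to stop CPAP for the test.

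Other stronger readings also lack support:

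- **Bias.** CPAP is prescribed alike in both arms, so the randomised comparison is not biased by it.
- **A stated loss of power.** This would need the share of the effect that survives on CPAP, which the documents do not give.
- **A mismatch with the treatment rationale.** The Discussion's "positive effect on the tone of oropharyngeal muscles and other soft tissues of the upper airway" might be taken as the mechanism under test. That sentence describes myofunctional therapy, which both arms receive, so it says nothing about the contrast between them.
- **Sizing from the compliance rule.** The rule allows some treatment nights with little or no CPAP. It does not say what happens on a scheduled test night.

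**Conclusion.** The point holds as a weakness in how a primary endpoint is specified. The text pairs daily CPAP with the only post-treatment AHI and fixes no CPAP condition for the recording. The week-12 value may therefore be residual or mixed, compared with a baseline that Table 1 places in the diagnostic range (assuming that the eligibility recording, or one like it, serves as baseline).

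The consequence is possible compression and added noise in the between-arm AHI difference, and a within-arm change that cannot be credited to rehabilitation. Its size cannot be derived from the documents. The bound below 5 events per hour, the 2-to-20 spread and the signal ratios all rest on stated assumptions. If the full protocol already requires off-CPAP testing at both times, one sentence settles the CPAP question. The choice between change score and baseline adjustment would still be worth fixing, because the article commits to repeated-measures ANOVA or its non-parametric variants and leaves adjustment optional.

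**What to change.** 1. State that the baseline and week-12 home sleep tests are recorded off CPAP in both arms, after the same short fixed CPAP-free interval agreed with the pulmonologist and the ethics committee.
2. Log CPAP use on each test night, and keep every recording in the intention-to-treat analysis whatever the log shows.
3. Whether or not CPAP is interrupted, compare the arms on week-12 AHI adjusted for baseline AHI (ANCOVA), in place of the group-by-time term of a two-time-point repeated-measures ANOVA.
4. If CPAP cannot be interrupted, label the endpoint residual AHI on CPAP and do not interpret the within-arm change as an effect of rehabilitation.

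The cost is one or a few nights without CPAP in patients with mild to moderate OSA, one field on the case report form, a change of protocol wording and an ethics notification. Under item 4 no CPAP is missed; only the label, the analysis wording, the interpretation and the test-night log change. No change to the sample size follows from this point.
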